## Abstract

Prolonged sitting leads to a slumped posture, which indirectly influences spinal curvature and increases low back and hamstring stiffness. Active rather than passive recovery is an effective way to reduce the risks associated with such prolonged inactivity. However, it remains to be investigated which of the exercises frequently used for this purpose, the trunk stability and foam rolling exercise, is more beneficial. This protocol study will compare the effects of foam rolling exercises on the recovery of impaired core and postural stability induced by core muscle fatigue and hamstring muscle stiffness with those of trunk stabilization exercises in sedentary adults. Twenty sedentary adults ranging in age from 25 to 44 years old, comprising 50% men and 50% women, will participate in a modified Abt’s trunk muscle fatigue protocol, then proceed with (1) active recovery in the form of trunk stabilization exercises, (2) active recovery in the form of foam rolling exercises, and (3) passive recovery, entails lying on a bed, respectively. Pre-fatigue, post-fatigue, and after all three recovery modalities, core and postural stability, and back and hamstring muscle flexibility will be evaluated using an inertial sensor system, and a posturography system. Muscle-fatigue conditions will be determined using electromyogram signals. Although the effects of foam rolling and trunk stabilization exercises can be attributed to different physiological mechanisms, the former releasing myofascial to improve flexibility and reduce muscle tension, the latter strengthening core muscles to stabilize posture, we hypothesize that both are equivalently effective in reducing the consequences of prolonged sitting.

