
As explained earlier, the mechanisms for the effects of trunk stabilization exercises and foam rolling exercises on core and postural stability are described differently. It is hypothesized that both exercises will induce a significant improvement in core and postural stability. If foam rolling is found to be an effective exercise for recovery of impaired core and postural stability, core-specific exercises may not be necessary in the workplace. This would lead to a reduction in training time (Zahiri et al., 2022), which is a positive aspect of workplace exercise. This study presents a protocol for the investigating the modeling of the process of muscle fatigue and recovery to provide an opportunity to identify suitable workplace exercises. The purpose of this study will be to compare the immediate effect of trunk stabilization exercises on recovery of impaired core and postural stability induced by fatigue with that of foam rolling exercises in sedentary adults.

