### 2.7 Statistical analysis

The statistical analysis will employ SPSS Statistics software (Version 24; IBM Corporation^©^, United States). To evaluate the normality of core and postural stability, as well as EMG variables, a Shapiro-Wilk test will precede any comparative analyses. For normally distributed data, a two-way ANOVA will be applied to explore the main effects of recovery modalities and time intervals, along with any potential interactions between these factors. The factors under consideration include the type of conditions [trunk stabilization exercises session, foam rolling exercise session, passive recovery] and testing time [T1: baseline, T2: immediately after modified Abt’s fatigue protocol, T3: immediately after recovery modalities, and T4: 15 min after recovery modalities]. To identify significant differences, Bonferroni *post hoc* comparisons will be conducted as necessary.

For non-normally distributed data, nonparametric tests will be utilized. Friedman’s test, followed by Dunn’s *post hoc* test, will be employed to compare core and postural stability, as well as EMG variables across testing times [T1, T2, T3, and T4]. The Kruskal-Walli’s test will be utilized for between-condition mentioned above comparisons at each testing time.

Data will be presented as mean ± standard deviation (SD). Effect sizes for both between-session and within-session comparisons of all quantitative variables will be evaluated using Cohen’s d coefficient: small effect (d < 0.2 and ηp2 = 0.01); moderate effect (d ≈ 0.5 and ηp2 = 0.06); and large effect (d > 0.8 and ηp2 = 0.14) (Cohen, 2013). The significance level (α) will be established at 0.05 for all statistical tests.

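### The abstract hypothesizes that the two exercises are equivalent, the introduction only that both improve stability; the planned difference tests can address the second but cannot confirm the first

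*Protocol article*

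**What the plan says.** The protocol article states two hypotheses.

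- **Abstract, last sentence:** "we hypothesize that both are equivalently effective in reducing the consequences of prolonged sitting". The two exercises compared are foam rolling and trunk stabilization.
- **1 Introduction, last paragraph:** "It is hypothesized that both exercises will induce a significant improvement in core and postural stability". Equivalence is not mentioned. The same paragraph adds that, if foam rolling turns out to be effective for recovery, "core-specific exercises may not be necessary in the workplace".

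The analysis is fixed in Section 2.7. For normally distributed data, "a two-way ANOVA will be applied to explore the main effects of recovery modalities and time intervals", together with their interaction (three conditions by four testing times). The follow-up is described as "To identify significant differences, Bonferroni" post hoc comparisons. The alternative branch reads "For non-normally distributed data, nonparametric tests will be utilized": Friedman with Dunn over time, and for the conditions a Kruskal-Wallis "test will be utilized for between-condition mentioned above comparisons at each testing time". Effect sizes will be reported, but no decision rule is attached to them. On error control, "The significance level (α) will be established at 0.05 for all statistical tests".

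Section 2.4 sizes the study with a repeated-measures F test: f = 0.25, alpha 0.05, power 0.80, correlation 0.70, epsilon 1. This gave seven subjects per trial, and the number was raised to 20, each tested in all three conditions.

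**The concern.** Every test in Section 2.7 has a null hypothesis of no difference. Rejecting it for the foam rolling versus trunk stabilization comparison would contradict a hypothesis of exact equality, though the difference might still be too small to matter. Failing to reject it leaves the question open. Without a margin, neither result can establish that the exercises are equivalent.

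What is at stake is what the trial may conclude. Of the possible results of the planned between-exercise tests, only a non-significant one looks like agreement with the abstract, and low power or a strict multiplicity correction makes that result more likely. The practical message, that foam rolling could stand in for core exercise at work, would be drawn next to such a result.

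**Working it through.** **1. What the stated sample size is for.** Section 2.4 does not give the numbers of groups and measurements, so I tried the plausible settings with the noncentral F, λ = f²·N·m/(1 − r).

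- Within-between interaction, 3 groups × 4 times (df = 6 and 3(N − 3)): at N = 19, λ = 0.0625·19·4/0.30 = 15.83 and power is 0.810; at N = 18 power is 0.781. Nineteen in total rounds up to 7 per group (21 in total, power 0.859), which matches the stated seven.
- Within factors, one group, 12 measurements: N = 8 gives power 0.825 and N = 7 gives 0.748, close to the stated seven.
- Within factors, one group: 3 measurements need 17 and 4 need 15, which do not match.

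Each variant powers the detection of a difference. The value f = 0.25 is an effect to be found, not a margin.

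**2. How informative a non-significant comparison would be.** Inputs from the protocol: n = 20 (all completing) and r = 0.70. My assumptions: a true foam rolling minus trunk stabilization difference of 0.3 to 0.5 SD, a Bonferroni family of three condition pairs, a two-sided test, one outcome at one time point, a simple paired comparison, and r = 0.50 as a sensitivity value.

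- SD of the paired difference = √(2(1 − r)) = √0.60 = 0.775 outcome SDs
- Standard error = 0.775/√20 = 0.173
- Noncentrality for 0.5 SD = 0.5/0.173 = 2.89, on 19 df
- Critical t = 2.093 at alpha 0.05, and 2.625 at 0.05/3

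Probability of a non-significant result (noncentral t):

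| True difference | r = 0.70, unadjusted | r = 0.70, Bonferroni | r = 0.50, unadjusted | r = 0.50, Bonferroni |
|---|---|---|---|---|
| 0.3 SD | 62% | 79% | 75% | 88% |
| 0.4 SD | 41% | 60% | 60% | 77% |
| 0.5 SD | 22% | 39% | 44% | 63% |

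The expected 90% CI half-width is t(0.95, 19) × SE = 1.729 × 0.173 = 0.30 SD at r = 0.70, and 0.39 SD at r = 0.50.

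**3. What an equivalence test could show with the same 20 people.** Paired TOST, one-sided alpha 0.05 on each side, true difference 0. The documents give no margin, so all margins are assumed.

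| Margin | Power, n = 20, r = 0.70 | Power, n = 20, r = 0.50 | N for 80% power, r = 0.70 |
|---|---|---|---|
| 0.3 SD | 10% | 1% | 59 |
| 0.4 SD | 44% | 12% | 34 |
| 0.5 SD | 74% | 39% | 22 |
| 0.6 SD | 91% | 65% | 16 |

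These figures use raw paired differences. An analysis adjusted for the post-fatigue value would have a different variance, and dropouts would lower the power.

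**The case against.** The strongest reply is that equivalence is not the operative objective. The word appears once, in the abstract. The Introduction's hypothesis is that both exercises improve stability, which the planned ANOVA and post hoc tests can address. The stated purpose is to compare the two exercises, and the abstract and Discussion ask which is more beneficial or effective; those are difference questions. All of this stands, and it limits the point to a conflict between the abstract and the rest of the plan.

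Three stronger readings are tempting, and the documents do not support them.

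- *A non-significant result will be read as equivalence.* A reader might infer this because no other planned result would look like support for the abstract. The protocol nowhere says so.
- *The replacement of core exercise is presented as an equivalence conclusion.* The statements in the Introduction and Discussion depend on foam rolling being effective, or on its activating the trunk muscles, not on its matching trunk stabilization. One may argue that replacement ought to require non-inferiority, but the protocol does not frame it that way.
- *The plan has no guard against two equally ineffective exercises.* Passive recovery is already the third condition, and the post hoc comparisons can set each exercise against it.

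What survives is that significant improvement in both arms would still not show equivalence, and reporting effect sizes without a margin does not decide the question. Nor is this a detail left to an unseen analysis plan: the article itself fixes the hypothesis, the tests and the sample-size basis, and they do not fit together.

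**Conclusion.** The point holds as a mismatch within the article. The abstract's equivalence hypothesis cannot be confirmed by any test in Section 2.7, and it differs from the Introduction's hypothesis, which those tests can address. The mismatch follows from the text alone. Its size rests on assumptions: with 20 completers and r = 0.70, an assumed true difference of 0.5 SD goes undetected 22% of the time unadjusted and 39% under an assumed three-pair Bonferroni step, and more often if the correlation or the difference is smaller. Whether 20 participants suffice for an equivalence claim depends on a margin that the protocol does not give. It does not follow that the whole trial fails to answer its question.

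**What to change.** Reconcile the abstract with the Introduction, before any results are seen, in one of two ways.

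**(a) Keep equivalence.** Name one primary outcome and one time point from the many listed under Section 2.5.3.1. State a margin in that outcome's units and justify it. Claim equivalence only if the paired 90% CI for foam rolling minus trunk stabilization lies wholly inside the margin and each exercise is superior to passive recovery. Note that ±0.5 SD, the smallest margin at which 20 people come near 80% power at r = 0.70, equals what Section 2.7 itself labels a moderate effect, so it would need a real argument.

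**(b) Drop equivalence.** Reword the abstract's hypothesis to match the Introduction and report the between-exercise difference with its CI.

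Under either option, add a sentence to Section 2.7: a non-significant ANOVA or post hoc comparison will not be read as equivalence, or as grounds for replacing core exercise.

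Option (b) costs a few words and one reported interval. Option (a) also needs the choice of a single outcome and a defended margin. With n = 20 only a wide margin could be confirmed, and a narrower one would need more people (34 at 0.4 SD, 59 at 0.3 SD, for 80% power at r = 0.70).

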## 1 Introduction

The modern lifestyle has led human societies toward a more sedentary existence (Stockwell et al., 2021; Chaudhary et al., 2024). The literature indicates that, in the future, three-fourths of all jobs worldwide will be sedentary (Khanzadeh et al., 2020). Sedentary behavior is described as “any waking activity with an energy expenditure of 1.5 METs or less while sitting, reclining, or lying down.” (Lassalle et al., 2021). Given that desk workers spend a considerable portion of their time seated, they could be potential targets for interventions aimed at reducing sedentary behavior (Barone Gibbs et al., 2018). This type of lifestyle is associated with musculoskeletal disorders, particularly when sitting is prolonged in uninterrupted bouts (Chia et al., 2015).

Prolonged sitting with ongoing contraction of the trunk muscles can lead to fatigue in the deep trunk muscles (Waongenngarm et al., 2016; Waongenngarm et al., 2018; Saiklang et al., 2022a; Saiklang et al., 2022b), which, in turn, can alter the neuromuscular system and result in core stability disorders (Jabłońska et al., 2021). This is because the neuromuscular system is responsible for creating the conditions necessary for adequate core stability through the coordinated contraction of the trunk muscles (Esmaeili and Askari, 2020).

Also, muscle fatigue can affect postural stability. Under fatigue, afferent feedback is disrupted, impairing joint proprioception and subsequently affecting somatosensory input (Tajali et al., 2022). Reduced efficiency in muscle contraction (Tajali et al., 2022), inadequate processing of sensory input, and compromised neuromuscular performance due to fatigue can disrupt both feedforward and feedback control of postural sway (Zemková et al., 2021a). Typically, a decline in postural stability is observed with muscular fatigue (Akulwar and Mulgaonkar, 2017). Especially, strategies of postural control can alter under muscle fatigue (Johanson et al., 2011). For instance, a study by Johanson et al. showed that the strategies used by fatigued individuals, when faced with increased postural demands, are similar to those utilized by individuals experiencing recurring low back pain. Fatigued healthy individuals exposed to a sudden perturbation have demonstrated an elevation in electromyographic amplitude, longer activation latencies, diminished muscle activity, and heightened co-contraction (Zemková et al., 2021a; Zemková et al., 2021b).

Another potential risk factor for impaired postural stability induced by prolonged sitting is the shortening of hamstring muscles due to repetitive keeping knees in flex (Shamsi et al., 2020). The hamstring’s structure includes a biceps femoris torso linked to the ischial tuberosity, an extension of the Sacro tuberous ligament, which crosses the os sacrum and attaches to the thoracolumbar fascia (Na’ima et al., 2019). Through this relationship, an increase in posterior pelvic tilt and reduction in lumbar lordosis due to the shortening of hamstring muscles can result in a flat back (Fatima et al., 2017; Na’ima et al., 2019; Encarnación-Martínez et al., 2023). Changes in the lumbar curvature can shift the center of gravity, potentially impairing postural stability (Shamsi et al., 2020; Encarnación-Martínez et al., 2023).

Given the fact that impaired core and postural stability strongly correlates with hamstring and trunk muscle corset conditions, it becomes crucial to restore optimal muscle capacity and efficiency. Physical exercises offer a potentially feasible option to reduce sedentariness at work without major disruption to office work practices. During core exercises, fatigued trunk muscles show an increase in EMG root mean square amplitude values. Specifically, two studies demonstrated that the abdominal drawing-in maneuver (Saiklang et al., 2021), as well as a combination of the abdominal drawing-in maneuver with supported dynamic lumbar extension (Saiklang et al., 2022a), increased the activation of the transversus abdominis (TrA) and internal oblique (IO) muscles. Additionally, the abdominal drawing-in technique led to higher activation ratios of TrA and IO compared to the rectus abdominis, highlighting its effectiveness in engaging these key muscles for spinal support. In another study, Abdelraouf and Abdel-Aziem demonstrated that core stability interventions can alter the recruitment patterns of core muscles (Abdelraouf and Abdel-Aziem, 2016), and effectively improve the fatigue resistance of these muscles, thereby restoring core stability (Zou et al., 2021). Trunk stabilization exercises aim to enhance and regain the coordinated contraction of both local and global muscles, improving control over the pelvis and lumbar spine (Richardson et al., 1999; Hodges, 2003). This also helps the trunk muscles regain their ability to fulfill the requirements of postural control (D’souza et al., 2022). Training with trunk stabilization exercises has shown significant improvements in core stability (Butcher et al., 2007; Sato and Mokha, 2009), and immediate improvements in static and dynamic balance (Kaji et al., 2010; Imai et al., 2011; Imai et al., 2014a; D’souza et al., 2022). Also, Szafraniec et al. demonstrated improvement in the mediolateral body balance after core exercise (Szafraniec et al., 2018). These effects were noticeable within a span of 30 min post-exercise and persisted for a minimum of 24 h. An enhanced automatic response in maintaining a stable upright posture was observed 24 h after the exercise session. However, there has been little discussion so far about the efficiency of trunk stability exercise in the recovery of core and postural stability during prolonged sitting at the workplace.

In recent times, foam rolling exercises have become increasingly popular due to their affordability, ease of use, and time-saving benefits (Kipnis, 2016; Biscardi et al., 2021; Zahiri et al., 2022). This method involves self-massage, where a person applies body weight on the foam roller to roll and compress specific muscle groups (Healey et al., 2014; Zahiri et al., 2022; Huang et al., 2024). Thus, instead of a trainer providing guidance, foam rolling can be carried out independently by an individual (Yektaei et al., 2023; Kalichman and David, 2017). These exercises help regulate muscle imbalances (Costa et al., 2017; Madoni et al., 2018; Egesoy et al., 2020; Hamzeh Shalamzari et al., 2020; Acar et al., 2022), alleviating muscle pain (Beardsley and Škarabot, 2015; Wiewelhove et al., 2019; Egesoy et al., 2020; Hendricks et al., 2020; Cabrera-Martos et al., 2022; Pagaduan et al., 2022) and joint stiffness (De Benito et al., 2019; Egesoy et al., 2020; Yokochi et al., 2024), and enhancing neuromuscular tone, flexibility (De Benito et al., 2019; Egesoy et al., 2020), and activity in the musculotendinous complex, promoting the maintenance of normal functional muscle length (Healey et al., 2014; Ateş et al., 2018; Egesoy et al., 2020; Nakamura et al., 2021). Using these exercises can lead to an expansion of range of motion and a reduction in muscle stiffness, without compromising muscle strength and athletic performance (Nakamura et al., 2021). The benefits of these exercises are attributable to changes in a muscle’s viscoelastic properties, decreasing fascial tenderness through the activation of Golgi tendon organs and mechanoreceptors, and possibly an increase in angiogenesis and vascular endothelial growth factor (Kurt et al., 2023; Behm and Wilke, 2019; Naderi et al., 2020). There are also psychological benefits, such as reducing anxiety and enhancing mood and relaxation (Kurt et al., 2023; Kerautret et al., 2021). 4-Week foam rolling exercises can be applied to improve the back and hamstring muscles’ range of motion (Sherer, 2013; Junker and Stöggl, 2015). Additionally, three 20-min sessions of foam rolling exercise following an exercise-induced muscle damage protocol, administered at 0, 24, and 48 h, improved passive and dynamic range of motion (MacDonald, 2013). The foam roller, due to its unstable surface, challenges the body to maintain stability and balance during exercise (Lukas, 2012; Junker and Stöggl, 2019). Furthermore, it appears that foam rolling exercises may contribute to restoring core and postural stability by reducing hamstring muscle stiffness and relaxing trunk muscles. However, only a limited number of studies have examined the effect of foam rolling exercises on core and postural stability parameters (Grabow et al., 2017; Junker and Stöggl, 2019; Alim, 2021).

As explained earlier, the mechanisms for the effects of trunk stabilization exercises and foam rolling exercises on core and postural stability are described differently. It is hypothesized that both exercises will induce a significant improvement in core and postural stability. If foam rolling is found to be an effective exercise for recovery of impaired core and postural stability, core-specific exercises may not be necessary in the workplace. This would lead to a reduction in training time (Zahiri et al., 2022), which is a positive aspect of workplace exercise. This study presents a protocol for the investigating the modeling of the process of muscle fatigue and recovery to provide an opportunity to identify suitable workplace exercises. The purpose of this study will be to compare the immediate effect of trunk stabilization exercises on recovery of impaired core and postural stability induced by fatigue with that of foam rolling exercises in sedentary adults.

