## 2 Materials and methods

### 2.1 Study design

The purpose of this pre- and post-quasi-experimental study will be to compare the immediate effect of trunk stabilization exercises on recovery of impaired core and postural stability induced by fatigue with that of foam rolling exercises in male and female sedentary adults. The protocol will be implemented and documented according to the Standard Protocol Items: Recommendations for Interventional Trials Statement (SPIRIT). The study design is provided in Figure 1. The research has obtained approval from both the ethics committee at the Faculty of Physical Education and Sport, Comenius University in Bratislava (Approval No. 5/2022), as well as the Ethics Committee of Kerman University of Medical Sciences (Approval No. IR. KMU.REC.1401.386). The study was also registered in the Clinical Trials system under the reference IRCT20221126056606N1.

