#### 2.5.2 Experimentation

The experiment involves 20 participants, each completing three sessions spaced 1 week apart. In each session, they will perform a modified Abt’s fatigue protocol, consisting of eight exercises targeting their core muscles. Subsequently, they undergo recovery modalities. Everything will remain the same throughout the sessions except the type of recovery modality, which will be varied (trunk stabilization exercises, foam rolling exercises, and passive recovery). The order of the recovery modalities will be counterbalanced to control for potential sequence effects. Data will be gathered from participants at three different time points:1. Pre-fatigue assessment (baseline measurement).2. Post-fatigue assessment (immediately following the fatigue protocol).3. Post-recovery modalities assessment (immediately and 15 min after the completion of active and passive modalities, respectively).

Participants will be tested by the same examiners at the same time.

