##### 2.5.5.3 Passive recovery

Participants will be required to do nothing and lie on a bed in a darkened room for a duration of 24 min between the pretest and posttest assessments (Seidi et al., 2019).

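### The hypotheses and purpose name no comparison with passive recovery, so recovery that would also occur at rest could satisfy them

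*Protocol article*

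**What the plan says.** The Introduction gives the hypothesis: "It is hypothesized that both exercises will induce a significant improvement in core and postural stability". It then attaches a practical consequence: "If foam rolling is found to be an effective exercise for recovery of impaired core and postural stability, core-specific exercises may not be necessary". The Abstract words the hypothesis differently: "we hypothesize that both are equivalently effective in reducing the consequences of prolonged sitting". Section 2.1 gives the purpose as follows: "compare the immediate effect of trunk stabilization exercises on recovery of impaired core and postural stability induced by fatigue with that of foam rolling exercises". None of these statements mentions passive recovery.

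The design does include it. Section 2.5.2 has each participant complete three sessions one week apart, with trunk stabilization, foam rolling or passive recovery in counterbalanced order. In the passive session (section 2.5.5.3) participants "lie on a bed in a darkened room for a duration of 24 min".

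Section 2.7 plans a two-way ANOVA with condition (three levels, one of them passive) and time (T1 baseline, T2 after fatigue, T3 immediately after recovery, T4 15 min later), their interaction, and Bonferroni comparisons. For non-normal data it plans Friedman and Dunn tests across the four times and a Kruskal-Wallis test between conditions at each time. It does not say which of these results decides whether an exercise is effective.

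**The concern.** The impairment is produced by a trunk-fatigue protocol of about half an hour, carried out shortly before the recovery modality. Some of it can be expected to fade with time alone. If it does, two exercises that add nothing to rest would each show improvement from T2, and their improvements would look alike. That pattern agrees with the hypothesis in the Introduction and with the one in the Abstract. It would also appear to support the workplace conclusion that core-specific exercises can be dropped. The data that separate an exercise effect from natural recovery are already collected in each participant's passive session, but no stated hypothesis uses them.

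**Working it through.** **Inputs.** From section 2.4: 20 participants in all three conditions, correlation among repeated measures r = 0.70, alpha 0.05. From section 2.7: four test times, hence 4 × 3 / 2 = 6 time pairs for Bonferroni (0.05 / 6 = 0.0083). Assumed: two-sided tests, one outcome variable, all correlations equal, and natural recovery of d SD from T2 to T3, identical in the three sessions. The article gives no value for d, so a range is shown.

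**The plan's own figure.** Section 2.4 reports seven subjects in each trial for f = 0.25, power 0.80 and r = 0.70. With noncentrality f² × N × m / (1 − r), a three-group, four-time within-between interaction needs N = 19 (power 0.810). Rounding up to equal groups gives 21 = 3 × 7 (power 0.859), which matches. A one-group within-factor test gives 17 with three measurements and 15 with four. This point uses only the N of 20 and the r of 0.70.

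**Within-session improvement with no effect beyond rest.** The standardized paired change is dz = d / √(2(1 − 0.70)) = d / √0.6. For d = 0.5, dz = 0.645 and the noncentrality is 0.645 × √20 = 2.89. Under equal correlations the changes in two sessions are uncorrelated, so the chance that both are significant is the square of the single chance.

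| d | One exercise, unadjusted | Both, unadjusted | One exercise, Bonferroni | Both, Bonferroni |
|---|---|---|---|---|
| 0.2 | 0.194 | 0.038 | 0.056 | 0.003 |
| 0.5 | 0.782 | 0.611 | 0.494 | 0.244 |
| 0.8 | 0.992 | 0.984 | 0.939 | 0.881 |

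A simulation of 20,000 trials agrees: both exercises significant in 3.6%, 61.5% and 98.5% unadjusted, and 0.3%, 24.8% and 88.1% with Bonferroni. At d = 0.5, moving r from 0.5 to 0.9 moves the joint unadjusted figure from 32% to 99%.

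**The same trials judged against rest.** The condition-by-time F test is significant in about 5%, and both exercises significantly beat rest in about 0.4%, at every d. A given exercise is falsely favoured in about 2.5%. These rates hold only if natural recovery is equal across sessions.

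**Power of the contrast with rest.** The difference between two changes has variance 4(1 − 0.70) = 1.2, so dz = d / √1.2. With 20 participants, power is 12%, 49% and 87% for extra recovery of 0.2, 0.5 and 0.8 SD.

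**Timing.** Passive recovery lasts 24 min. The trunk programme in section 2.5.5.1 is 3 exercises × 5 repetitions × (5 + 5 + 10) s = 300 s, or 5 min. Foam rolling in section 2.5.5.2 is six areas × 30 s = 3 min, or 6 min if every area is done on both sides. As described, T3 therefore falls about 18 to 21 min later after fatigue in the passive session (24 − 6 to 24 − 3). T4 in the exercise sessions falls at about 18 to 21 min (3 + 15 to 6 + 15), near the passive T3 at 24 min, not counting time spent on assessments.

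**The case against.** The Introduction sentence is a hypothesis with no interval, test or decision rule, and saying that an exercise induces improvement fits a controlled comparison as well as a within-session one. Passive recovery is part of the framing, the design and the analysis. In the parametric branch, equal recovery everywhere would usually appear as a shared time effect without an interaction. The rank branch also compares conditions, passive included, at each time. An analysis plan that is not shown may name the deciding contrast. The size rests on an undocumented natural recovery, and the unadjusted joint figures ignore the planned Bonferroni step.

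Much of this stands. A reader might infer that the protocol formally counts an exercise as successful once stability improves within its session, or that the trial lacks a control. The documents support neither. Nor do they say why the passive session is run, so it cannot be claimed that it was added to handle natural recovery.

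The wording of the hypotheses and the conclusion hung on them remain. Both are stated in this article, and an analysis plan works from the hypothesis it is given. The Discussion treats the superiority of active over passive recovery as widely accepted and does not make it the question to be tested. The interaction is to be explored, but nothing depends on it. In the rank branch, Friedman looks at time and Kruskal-Wallis at levels at single times, so neither tests whether change differs from change at rest.

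**Conclusion.** The concern holds as a fault in the stated hypotheses and purpose and in the absence of a deciding contrast with rest. The control condition is present. Significant and similar gains in both exercise sessions would satisfy the hypotheses with no effect beyond rest. How often this would happen runs from negligible to very likely: about 0.3% to 88% with Bonferroni, or 4% to 98% unadjusted, for natural recovery between 0.2 and 0.8 SD. This assumes one variable, r = 0.70 and equal recovery in all sessions.

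It would go too far to say that natural recovery will be reported as effectiveness, because the planned ANOVA could show the authors otherwise. It would also go too far to say that a contrast with rest, on the schedule as written, is clean. If recovery continues with time, the longer passive period biases the T2-to-T3 contrast against the exercises.

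**What to change.** Restate the hypotheses in the Abstract and Introduction, and the purpose in the Introduction and section 2.1, so that an exercise is called effective for recovery only if its change from T2 exceeds the change in the participant's own passive session. In section 2.7, test this by the modality-by-time interaction and paired contrasts with passive recovery; in the rank branch, use a paired rank test on the change scores. Report within-session change as descriptive.

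Before that, reconcile the durations in sections 2.5.5.1 to 2.5.5.3, or define the contrast at matched time since the end of the fatigue protocol. If the schedule stays as described, exercise T4 against passive T3 is the closest existing pair.

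The restatement needs no new participants or visits. Matching time may require a change in when assessments are taken. The main cost is power: at 0.5 SD the contrast with rest has about 49%, against 78% for the unadjusted within-session test, and at 0.8 SD it has about 87% against 99%.
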